## Trial interventions

### Open reduction and internal fixation

ORIF, stabilization without fusion, is one of the surgical interventions in the treatment of Lisfranc injury. After surgical exposure any dislocation will be reduced and fixation of the Lisfranc injury will be achieved by osteosynthesis. Osteosynthesis of the first three TMT joints or intercuneiform joints will preferably be done by using bridge plate (variable angle locking plate and/or locking plate and/or dynamic compression plate—3.5 mm, 2.7 mm or 2.4 mm) and/or trans articular screw osteosynthesis (4.0 mm cannulated screws and/or solid small fragment screws and/or HCS). For fixation TMT4 and/or TMT5 K-wires (1.6–2.0 mm) will be used instead.

### Primary arthrodesis

PA, stabilization by fusion, is the other surgical intervention of choice in the treatment of Lisfranc injury. After surgical exposure, cartilage of the involved unstable joints ray 1–3 of the Lisfranc injury will be removed and after reduction, fixation will be done by osteosynthesis with bone graft if necessary. Osteosynthesis will be done by using bridge plate (variable angle locking plate and/or locking plate and/or dynamic compression plate—3.5 mm, 2.7 mm or 2.4 mm) and/or trans articular screw osteosynthesis (4.0 mm cannulated screws and/or solid small fragment screws and/or HCS).

The tarsometatarsal joints 4–5 are essential joints to remain dynamic and the consensus is to fix these using some temporary fixation device, mostly K-wires if remaining dislocated after arthrodesis of the first 3 TMT joints.

### Potential harms

The sponsor will suspend the study if there are adequate motives to suppose that continuation of this trial will harm a participant’s safety or well-being. This is in accordance with section, subsection 4 of the Medical Research Involving Human Subjects Act (WMO). Subsequently the sponsor will inform the licensed Medical Ethical Board without unreasonable delay of a temporary halt including the reason for such an action. The study will be suspended while waiting for a further positive submission by the Medical Ethical Board. All the included participants of the study kept informed by the CI. The adverse events (AEs) of the study are defined as any unwanted finding occurring to an included participant during the study, whether related to the study or not. This AEs are reported spontaneously by the included participants or observed by the LI or side investigator of each medical institution. All of the serious adverse events will be announced in compliance with the guidance from The Central Committee on Research Involving Human Subjects (CCMO).

## Outcomes

### Primary outcome

The primary outcome is the quality of life as defined by the EQ-5D-5L questionnaire. The EQ-5D-5L questionnaire is used to assess the health-related quality of life in this study. This questionnaire consists of a descriptive method including five health related measurements and a Visual Analogue Scale (VAS) that documented the participants self-determined healthiness. Due to an algorithmic program that is based on the values obtained from the Dutch population the index scores for each included participant of the study can be measured. Subsequently, to calculate the QALY these index scores will be combined with the length [27].

### Secondary outcomes

Secondary outcomes are the differences in the amount and type of secondary procedures (including removal of osteosynthesis materials). The most important complications are post-traumatic arthritis, infection, persistent instability, non-union and foot deformity (pes planovalgus). The frequency of all complications will be measured using post-surgery follow-up visits. The differences in objective and subjective functional outcomes; active range of motion as determined by the online questionnaires: American Orthopaedic Foot and Ankle Society Score (AOFAS), Short Form Health Survey (SF-12), and Foot and Ankle Disability Index (FADI). The range of motion will also be measured at the clinical follow-up visits. The difference in alignment of the foot on weight-bearing X-rays (stability) which will be measured at the clinical follow-up moments. Secondary economic outcomes are the patient, family and societal health care costs, and the cost-effectiveness as measured with the online Medical Consumption Questionnaire (MCQ) and Productivity Costs Questionnaire (PCQ).

## Statistical analysis

### Descriptive statistics

Baseline patient characteristics will be described stratified by group allocation. Continuous variables will be summarized using mean and standard deviation (SD) or as median and first and third quartile. Categorical variables will be summarized as count and percentage.

Missing data will be imputed using stochastic regression imputation, using predictive mean matching to draft the values to be imputed, as this is more robust to misspecification of the imputation model and more appropriate for non-normally distributed continuous variables.

All analyses of the primary and secondary study parameters will be analysed in according with the intention to treat principle. A p-value of ≤ 0.05 will be considered to indicate statistical significance. All analyses will be performed using IBM SPSS version 25 or later.

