### Sample size and feasibility

The primary outcome is quality of life over the follow up period, quantified using the EQ-5D-5L score. The longitudinal analysis will include multiple observations per patient, but it is unclear how strong consecutive measurements are correlated. For that reason, we performed a sample size calculation for a cross-sectional contrast between the two groups, so that even with near-perfect correlation, we would have sufficient power to detect a clinically meaningful difference.

The estimated standard deviation (SD) of the EQ-5D-5L scores is 0.15. To be able to have sufficient statistical power (i.e., 80%) to detect a clinically meaningful difference in QoL of 0.08 points, we need to include 56 patients per group, or 112 in total. We estimate, based on previous experience, that we would need to screen approximately 190 patients to find 112 patients eligible and willing to participate.

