### Primary study parameter

EQ-5D-5L scores after treatment will be compared between groups using a linear mixed-effects regression model to account for clustering of multiple observations within each patient. Both absolute differences between groups, such as the difference in slope over time will be estimated. All parameters will be reported including 95% confidence interval. Additionally, we will add potential confounders as covariates to the model, irrespective of qualitatively determined baseline imbalance. We will add body mass index (BMI), age, and sex.

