## Economic evaluation

A trial-based economical evaluation will be completed from a societal and healthcare point of view with a total follow-up period of 24 months, and this evaluation is in line with the Dutch guidelines for health economical evaluation [28]. The Dutch costing manual is the source for the valuation of the cost prices [27]. The so called ‘friction cost method’ will be calculating the amount of absence of work of each included participant in this study. This ‘friction cost method’ is recommended by the Dutch manual for costing [29]. The cost-effectiveness in this study will be measured in societal cost per QALY, as based on the EQ-5D-5L questionnaire. Subsequently the sensitivity and the bootstrap analysis will be conducted to notice possible uncertainty. To visualize the chance of the cost-effectiveness of the two interventions cost-effectiveness acceptability curves will be constructed. Subsequently, sensitivity analyses will be performed on the data input for testing the strength of the study results. Besides, in accordance with the Dutch guidelines for economic evaluations as well as the ISPOR guidelines, a budget-impact analysis (BIA) will be performed [30].

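### The named imputation method draws each missing value once and no pooling is stated, so standard errors for the questionnaire outcomes will be too small

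*Protocol article*

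**What the plan says.** The Descriptive statistics section of the protocol article names one missing-data method: "Missing data will be imputed using stochastic regression imputation, using predictive mean matching to draft the values to be imputed". Its reasons for predictive mean matching are robustness to a misspecified imputation model and suitability for non-normal variables. The sentence is not limited to any variable. It is followed directly by rules that apply to every analysis: "All analyses of the primary and secondary study parameters will be analysed in according with the intention to treat principle", and "A p-value of ≤ 0.05 will be considered to indicate statistical significance".

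Under Primary study parameter, "EQ-5D-5L scores after treatment will be compared between groups using a linear mixed-effects regression model". Both the absolute difference between groups and the difference in slope over time are to be estimated, and "All parameters will be reported including 95% confidence interval". Secondary study parameters applies a similar model to the continuous secondary questionnaire scores. Under Economic evaluation, "Subsequently the sensitivity and the bootstrap analysis will be conducted to notice possible uncertainty".

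No section mentions multiple imputation, a number of imputed data sets, pooling or a variance correction.

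**The concern.** Stochastic regression imputation is the usual name for replacing each missing value once by a prediction plus random noise. Predictive mean matching changes how the value is drawn (from an observed donor with a similar prediction), not how many times. The reasons given concern how realistic the imputed values are, not how uncertain they are.

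A model fitted to one completed data set counts drawn values as if they were measurements. It therefore credits the trial with information that it does not have: standard errors come out too small, p-values too low, and 95% intervals cover less than 95%. The primary comparison is exposed, in a trial that presents itself as the first with enough power to settle the choice between the two operations. The exposure is also avoidable. A likelihood-based mixed model already uses every observed visit and is valid under missing at random without imputing outcomes.

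**Working it through.** **Inputs from the protocol article.** SD: "The estimated standard deviation (SD) of the EQ-5D-5L scores is 0.15". Target difference: "to detect a clinically meaningful difference in QoL of 0.08 points". Also 80% power, 56 per group, 1:1 allocation, significance level 0.05, and five post-surgery questionnaires (8 and 12 weeks; 6, 12 and 24 months).

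**Assumptions, because the article gives no figure.** Missing by 24 months: 10%, 20% or 30%. Within-patient correlation: 0.4 or 0.7 (exchangeable), since the sample-size section says that the correlation is unclear.

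**The plan's own figure.** n per group = 2(1.960 + 0.842)² × 0.15² / 0.08² = 55.2, rounded up to 56. At 56 per group the power is 80.6%. The stated size is reproduced with a two-sided test, and this point does not change it.

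**Direction, by formula.** Take one time point, a fraction f missing completely at random, and predictors that explain a share R² of the variance. After one draw per missing value, the ratio of true to reported variance of the group difference is approximately

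R² + (1 − R²) × [1/(1 − f) + f].

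The term 1/(1 − f) is the loss of information, and f is the noise added by the draw. The ratio exceeds 1 whenever f > 0 and R² < 1. The true error of the nominal 5% test is 2 × [1 − Φ(1.96/√ratio)]. With f = 0.2:

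| R² | Variance ratio | SE ratio | True error |
|---|---|---|---|
| 0 | 1.250 + 0.200 = 1.450 | 1.204 | 10.4% |
| 0.5 | 0.5 + 0.5 × 1.450 = 1.225 | 1.107 | 7.7% |
| 0.7 | 0.7 + 0.3 × 1.450 = 1.135 | 1.065 | 6.6% |

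The first row is an extreme, in which earlier scores say nothing about later ones.

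**Size for the contrasts that the plan estimates, by simulation.** No true group difference, 56 per arm, five visits, SD 0.15, monotone dropout completely at random, treatment arm and earlier scores in the imputation model, one draw per missing value, 2000 runs per scenario. The average over follow-up was tested on patient means and the slope on per-patient slopes. On balanced completed data, the group effect of a random-intercept mixed model equals the comparison of patient means. The ranges cover both correlations and repeated independent runs:

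| Missing by 24 months | Average over follow-up | Difference in slope | 24-month contrast |
|---|---|---|---|
| 10% | 5-6% | 6-7% | 6-7% |
| 20% | 6-8% | 10-11% | 8-10% |
| 30% | 6-8% | 12-14% | 9-13.5% |

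For the average over follow-up, the reported standard error was 0.94-0.97, 0.90-0.95 and 0.88-0.93 of the true one at 10%, 20% and 30% missing. Simulation error near 5% is √(0.05 × 0.95/2000) = 0.5 percentage points (one standard error), so the 5-6% at 10% missing is barely distinguishable from nominal. One-draw stochastic regression and one-draw predictive mean matching behaved alike.

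**Check of the remedy.** Multiple imputation (10 data sets, Rubin's rules, 1000 runs) gave 4.0-5.5% for the follow-up average and the 24-month contrast in all scenarios, with a reported-to-true SE ratio of 0.96-1.04.

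**The case against.** **The word single is not in the text.** The article does not say that only one data set is created, and a condensed article may leave the number of imputations and the pooling rule to a fuller document. It does, however, name a method, and that method conventionally means one draw. If pooling was intended, the published sentence describes something else and still needs correcting. It remains true that one draw is an inference from the method's name and the silence on pooling.

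**A reader might lead with the 24-month figures or the 10.4%.** The documents do not support that. The outcome is quality of life over the whole follow-up period, and no section makes the 24-month contrast primary. The 10.4% needs R² = 0, which is implausible when up to four earlier post-surgery scores predict the last one.

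**A reader might infer that every secondary result is biased to the same degree.** Late complications and re-interventions are also found by screening patient files at each follow-up (Data collection and processing), and radiographs are taken at the follow-up visits. Their missingness may be much lower than that of e-mailed questionnaires, and it is not given.

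**A reader might infer that the cost-effectiveness uncertainty is understated.** That follows only if the data are imputed once and then resampled. If imputation is repeated within each bootstrap sample, the uncertainty is carried through. Economic evaluation does not state the order.

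**Missingness may be low.** Patients are telephoned when a questionnaire is not completed within 5 days. At 10% missing, the inflation of the follow-up average is small. This limits the size of the problem but does not make the stated method valid.

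**Conclusion.** The concern holds for the questionnaire outcomes analysed by mixed models: EQ-5D-5L and the continuous secondary scores. As written, the method makes their tests and intervals anti-conservative. The direction is certain if each missing value is drawn once and the completed data are analysed as observed. The size is conditional. Under 10% to 30% missing by 24 months, true error is about 5-8% for the difference averaged over follow-up (95% intervals covering about 92-95%) and about 6-14% for the difference in slope (covering about 86-94%). The slope suffers more because it leans on the late visits, where most values are missing. These figures assume dropout completely at random and exchangeable correlation of 0.4 or 0.7. They were simulated for EQ-5D-5L and carry over to the other scores in direction rather than in exact size.

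For the binary endpoints and the bootstrap the effect is open, for the reasons given above. The sample size is unaffected, and no bias in the point estimates is shown.

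**What to change.** Before the data are analysed, replace the imputation sentence with rules to this effect:

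- Fit the linear mixed models for EQ-5D-5L and the continuous secondary scores to all observed scores, without imputing outcomes, and state the missing-at-random assumption.
- Where imputation is still needed (covariates such as BMI, binary endpoints, costs, QALYs), use multiple imputation by predictive mean matching, state the number of imputations, and pool with Rubin's rules.
- In the economic evaluation, state how imputation and bootstrap are combined so that imputation uncertainty reaches the intervals and acceptability curves.

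If several pooled imputations were intended all along, the second rule is only a correction of wording. The cost is a few sentences of text and slightly wider intervals. No further patients, visits or data are needed.

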### Sample size and feasibility

The primary outcome is quality of life over the follow up period, quantified using the EQ-5D-5L score. The longitudinal analysis will include multiple observations per patient, but it is unclear how strong consecutive measurements are correlated. For that reason, we performed a sample size calculation for a cross-sectional contrast between the two groups, so that even with near-perfect correlation, we would have sufficient power to detect a clinically meaningful difference.

The estimated standard deviation (SD) of the EQ-5D-5L scores is 0.15. To be able to have sufficient statistical power (i.e., 80%) to detect a clinically meaningful difference in QoL of 0.08 points, we need to include 56 patients per group, or 112 in total. We estimate, based on previous experience, that we would need to screen approximately 190 patients to find 112 patients eligible and willing to participate.

### Primary study parameter

EQ-5D-5L scores after treatment will be compared between groups using a linear mixed-effects regression model to account for clustering of multiple observations within each patient. Both absolute differences between groups, such as the difference in slope over time will be estimated. All parameters will be reported including 95% confidence interval. Additionally, we will add potential confounders as covariates to the model, irrespective of qualitatively determined baseline imbalance. We will add body mass index (BMI), age, and sex.

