### Study design

The BFF Study is a nationally prospective multicenter, randomized controlled trial (RCT) performed in the Netherlands. In total, 13 medical institutions in the Netherlands will enroll patients during a 24 months period, and the enrolment is stared at June 2020. The participating institutions of “The BFF Study” are defined in the Additional file 2.

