### Randomization and blinding

After given written informed consent, participants will be randomized in a 1:1 ratio to PA or ORIF, using randomization stratified by the center with random permuted block sizes of four patients. This randomization will be performed using a web-based computer (L-DOT) directed randomization. This randomization tool was developed by the centre of data and information management at the Faculty of Health, Medicine and Life Sciences of Maastricht University and MUMC+ (MEMIC). A unique study record number will be generated, and the allocation will be disclosed. Due to the comparison of outpatient-based and surgical treatment strategies in this study, blinding to the treatment allocation for participants and medical staff is not possible. A specialized independent statistician will analyze the data blinded for treatment allocation.

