### Secondary study parameters

Binary secondary outcome variables (i.e., having received any secondary surgical procedure, experienced any type of complication, showing stability and alignment on weight bearing radiographs) will be compared between groups using Pearson’s Chi-squared test. In case of expected cell counts of less than five we will use Fisher’s Exact test.

Continuous secondary outcomes (i.e., scores on the AOFAS, SF-12, FADI, MCQ, and PCQ) will be analysed using a linear mixed-effects regression model, similar to the analysis of the primary study parameter.

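### Centre stratifies the randomisation but is not in the mixed models for the primary and continuous secondary outcomes, so their tests are somewhat conservative if centres differ

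*Protocol article*

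**What the plan says.** The Randomization and blinding section of the protocol article allocates patients 1:1, "using randomization stratified by the center with random permuted block sizes of four patients". The Study design section gives the number of strata: "In total, 13 medical institutions in the Netherlands will enroll patients".

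Under Primary study parameter, EQ-5D-5L scores are compared with a "linear mixed-effects regression model to account for clustering of multiple observations within each patient". The covariates are then listed: "We will add body mass index (BMI), age, and sex". Under Secondary study parameters, continuous outcomes use a "linear mixed-effects regression model, similar to the analysis of the primary study parameter", while binary outcomes "will be compared between groups using Pearson’s Chi-squared test", with Fisher's exact test as the fallback for small expected counts.

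No section of the article names centre as a fixed effect, a random effect or a stratum in any analysis.

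**The concern.** Blocking within centre makes the arms alike on centre, so differences between centres largely drop out of the true sampling variance of the treatment contrast. If the model has no centre term, those differences stay in the residual. The reported standard error then exceeds the true one, confidence intervals are wider than they need be, and the test rejects less often than its nominal 5% under the null.

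Centre differences are plausible here, since the intervention sections leave the choice among plates and screws, and the use of bone graft in the arthrodesis arm, to the operating team. At stake is some precision that the stratification made available. The plan adjusts for three variables that were not stratified on and leaves out the only one that was.

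**Working it through.** **Inputs.** From Sample size and feasibility: SD 0.15, difference 0.08, 80% power, 56 per arm, 112 in total. From Descriptive statistics: significance level 0.05, taken as two-sided. From Study design: 13 centres, so 112/13 = 8.6 patients per centre on average. Assumed, because the article gives no value: centre ICC ρ from 0 to 0.15. Also assumed: 0.15 is the total SD, including variation between centres.

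**The plan's own figure.** n per arm = 2 × (1.960 + 0.842)² × 0.15² / 0.08² = 55.2, rounded up to 56. The stated sample size reproduces. With 56 per arm, SE = 0.15 × √(2/56) = 0.02835 and power = Φ(0.08/0.02835 − 1.96) = 80.6%. A t-based calculation gives 79.9%.

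**Effect of leaving centre out.** With exact balance within centres:

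- SE reported without centre: 0.02835
- True SE: 0.02835 × √(1 − ρ)
- Type I error without centre: 2 × [1 − Φ(1.96/√(1 − ρ))]
- Power without centre: Φ((0.08/0.02835 − 1.96)/√(1 − ρ))
- Power with centre: Φ(0.08/(0.02835 × √(1 − ρ)) − 1.96)

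Worked at ρ = 0.10: true SE = 0.02835 × 0.9487 = 0.02689. Type I error = 2 × [1 − Φ(2.066)] = 3.9%. Power without centre = Φ((0.08 − 0.05557)/0.02689) = 81.8%. Power with centre = Φ(2.975 − 1.96) = 84.5%.

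| Assumed ICC | SE reported / true | Type I error, no centre | Power, no centre | Power, with centre | Points forgone |
|---|---|---|---|---|---|
| 0 | 1.000 | 5.0% | 80.6% | 80.6% | 0 |
| 0.02 | 1.010 | 4.8% | 80.8% | 81.4% | 0.5 |
| 0.05 | 1.026 | 4.4% | 81.2% | 82.5% | 1.3 |
| 0.10 | 1.054 | 3.9% | 81.8% | 84.5% | 2.7 |
| 0.15 | 1.085 | 3.4% | 82.5% | 86.5% | 4.0 |

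The last column is taken before rounding. At ICC 0.02 the rounded powers would suggest 0.6.

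**Check by simulation.** Exact balance is an idealisation, because blocks of four with about nine patients per centre leave incomplete blocks. Simulations used 13 unequal centres, blocks of four and N = 112.

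- Random centre intercept against no centre term (6,000 runs per scenario). Type I error without and with centre: 5.2 and 5.4% at ICC 0, 4.4 and 5.1% at 0.05, 3.9 and 4.8% at 0.10, 3.8 and 5.2% at 0.15. Power without and with centre: 80.4 and 80.8%, 79.8 and 81.2%, 81.2 and 83.5%, 82.0 and 85.4%.
- Centre as fixed effects (10,000 runs per scenario). At ICC 0.10 power is 81.3% without and 82.8% with centre, a gain of 1.5 points. At ICC 0 to 0.02 the fixed terms cost 0.3 to 0.6 points.

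Monte Carlo error on a power near 80% is √(0.8 × 0.2/6,000) = 0.5 points. The direction is confirmed. At ICC 0.10 and 0.15 the simulated gains from a random intercept, 2.3 and 3.4 points, are somewhat below the formula's 2.7 and 4.0.

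**The case against.** The strongest reply is that nothing is invalid. The error is conservative, so type I error stays at or below 5%. Power without centre is not below what the sample-size section promises: if 0.15 is the total SD, it runs from 80.6 to 82.5% over the assumed range. The loss exists only against a better model, it depends on an ICC that the article does not give, and it vanishes as that ICC approaches zero. The figures also describe a single cross-sectional contrast, without the repeated measures and covariates of the planned model. All of this stands, and it limits the weight of the point.

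A second reply is that this is a journal article, and that the full protocol or an analysis plan may specify centre. That is possible, and it rules out saying that centre is absent from every planned analysis. It does not remove the point, because the article states a clustering level and a covariate list, and centre is in neither.

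Two stronger readings are tempting. A reader might infer that the omission leaves the trial underpowered or its primary test invalid. The arithmetic shows neither. A reader might also infer that the chi-squared and Fisher tests must be replaced. The documents do not support that. No loss has been shown for any binary outcome. With about 8.6 patients per centre and complication risks that the article itself describes as low, many Cochran-Mantel-Haenszel strata could be uninformative, and a mixed logistic model could be unstable.

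**Conclusion.** The point holds as a modest matter of efficiency and of consistency between design and analysis. As described in the article, the primary and continuous secondary mixed models leave out the sole stratification factor. Over an assumed ICC of 0 to 0.15, the reported standard error is 0 to 8.5% too large and the type I error runs from 5.0 down to 3.4%. The power forgone is 0 to about 4 points, which is an upper figure given incomplete blocks. Up to an ICC of 0.05 it is little more than one point. These sizes rest on the assumed ICC, on 0.15 being the total SD, and on the cross-sectional approximation. That centre is missing from the stated models rests on the text alone.

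**What to change.** Add centre as a random intercept, above the patient level, to the primary mixed model and to those for the continuous secondary outcomes. A random intercept is preferable to 12 fixed centre terms with about nine patients per centre. In simulation it carried no power penalty when centre had no effect, whereas fixed terms cost a little.

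For the binary outcomes the planned tests can stay. A centre-stratified analysis such as Cochran-Mantel-Haenszel may be added as a sensitivity analysis, with a note that centres without events contribute nothing.

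The cost is one term per mixed model and a sentence or two in the plan, written before the data are unblinded. No new data are needed and the sample size does not change.

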### Follow-up procedure

Follow-up will consist of clinical follow-up at 2 weeks and clinical follow-up and e-mail questionnaires at baseline at 8 and 12 weeks, and 6, 12 and 24 months after surgery (Fig. 1). After care will be the same for all patients, namely plaster cast immobilization or Air Walker for 8 weeks in total. Plaster cast immobilization or Air Walker will be non-weight bearing for 4 weeks followed by weight bearing for another 4 weeks.

All questionnaires will be digital. Enrolled patients will receive a link by e-mail at the preset follow-up moments to fill in before the standard follow-up moment at the outpatient clinic occurs, except at 2 weeks post-surgery. These messages are regulated by Castor Electronic Data Capture.

Radiographs will be performed each follow up period and interpreted as “aligned or not aligned” using previously mentioned alignment criteria for that specific follow-up moment.

To promote participants retention and complete follow-up the patients are called by the CI if the participant does not fill in the questionnaire within 5 days after invitation.

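### The primary mixed model leaves out baseline EQ-5D-5L although a baseline questionnaire is scheduled; adding it would gain precision, but leaving it out is not an error

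*Protocol article*

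**What the plan says.** Under Primary study parameter, the protocol article sets out a linear mixed-effects model whose outcome is the EQ-5D-5L score after treatment. It plans covariates whether or not the arms look imbalanced at baseline, and names them: "We will add body mass index (BMI), age, and sex". Baseline EQ-5D-5L is not among them. Because the outcome is restricted to post-treatment scores, on a plain reading baseline is not in the outcome vector either.

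Follow-up procedure schedules "e-mail questionnaires at baseline at 8 and 12 weeks, and 6, 12 and 24 months after surgery". Secondary study parameters applies a similar mixed model to the continuous secondary scores.

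Sample size and feasibility gives the planning figures: "The estimated standard deviation (SD) of the EQ-5D-5L scores is 0.15"; the aim is to "detect a clinically meaningful difference in QoL of 0.08 points" with 80% power; and "we need to include 56 patients per group, or 112 in total". The calculation is for a single cross-sectional contrast and takes no credit for baseline or for repeated measurement.

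Economic evaluation says: "The cost-effectiveness in this study will be measured in societal cost per QALY, as based on the EQ-5D-5L questionnaire". The article does not describe how the QALY difference between arms will be estimated.

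**The concern.** The baseline value of a continuous outcome is ordinarily a leading candidate covariate. The plan already accepts prespecified adjustment for prognostic variables and has fixed which ones to use, so this is a choice made in the text and not a detail left to a later document. The choice omits a variable the trial appears set to collect.

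Two things are at stake. First, precision: if baseline and follow-up scores are correlated, adjustment reduces the residual variance and narrows the confidence interval with no extra patients. Second, chance imbalance: with 56 patients per arm, the baseline means can differ by a few hundredths of a point, and part of that difference carries into the estimated effect of the trial that was actually run. Because the model is reused for the secondary scales, the same loss applies to any of them that is measured at baseline.

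**Working it through.** **Inputs from the protocol article.** SD 0.15, difference 0.08, power 80%, 56 per arm (Sample size and feasibility); 1:1 allocation (Randomization and blinding); "A p-value of ≤ 0.05 will be considered to indicate statistical significance" (Descriptive statistics). Sidedness is not stated. Two-sided is assumed because it reproduces the stated number; one-sided would give 44 per arm.

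**Inputs not in the article.** The correlation r between baseline and follow-up EQ-5D-5L is not given and is shown over a range. The baseline SD is assumed to be 0.15, the same as at follow-up.

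**Step 1: the plan's own figure.**
- n per arm = 2 × (1.960 + 0.842)² × (0.15/0.08)² = 55.2, rounded up to 56, or 112 in total. The stated figure is reproduced.
- SE = 0.15 × √(2/56) = 0.0283. Power = Φ(0.08/0.0283 − 1.96) = 80.6% by the normal approximation (79.9% by the t-test).

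**Step 2: the same contrast with baseline as a covariate.** Residual SD = 0.15 × √(1 − r²), so SE = 0.0283 × √(1 − r²).

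| Assumed r | SE | Variance reduction | Power at 56 per arm | n per arm for 80% |
|---|---|---|---|---|
| 0 (no gain) | 0.0283 | 0% | 80.6% | 56 |
| 0.1 | 0.0282 | 1% | 81.0% | 55 |
| 0.2 | 0.0278 | 4% | 82.1% | 53 |
| 0.3 | 0.0270 | 9% | 84.1% | 51 |
| 0.4 | 0.0260 | 16% | 86.8% | 47 |
| 0.5 | 0.0245 | 25% | 90.3% | 42 |

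**Step 3: chance imbalance.** The baseline difference between arms has SE 0.0283. With equal SDs, the share carried into an unadjusted follow-up contrast is r times the imbalance.

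| Assumed r | Shift from a one-SE imbalance | As a share of 0.08 | 95% range of the shift |
|---|---|---|---|
| 0.1 | 0.003 | 3.5% | ±0.006 |
| 0.3 | 0.009 | 11% | ±0.017 |
| 0.5 | 0.014 | 18% | ±0.028 |

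**Step 4: allowing for repeated measurement.** The planned model uses five post-surgery questionnaires. For the mean of five scores with a common correlation ρ between follow-ups and complete data (both assumptions), the variance factor is (1 + 4ρ)/5. With a baseline correlated r = 0.3 with each follow-up, it becomes (1 + 4ρ)/5 − 0.09.

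| Assumed ρ | Power without baseline | Power with baseline, r = 0.3 |
|---|---|---|
| 0.5 | 95.4% | 97.7% |
| 0.7 | 89.9% | 93.2% |
| 0.9 | 83.7% | 87.2% |

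Adjustment still helps here, but from a higher starting point than 80.6%.

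**The case against.** The strongest reply is that nothing in the plan is wrong. Under 1:1 randomisation the model without baseline is unbiased on average, and its confidence interval already allows for chance imbalance. The sample size reproduces without baseline adjustment. All of this stands.

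A reader might infer that the trial has no power to spare. The article does not support that: the number was deliberately based on one cross-sectional contrast, so the repeated measures may add power, as step 4 shows under its assumptions.

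The gain may also be small. Patients enter within six weeks of an acute injury, so baseline may largely reflect acute disability and predict later scores weakly. At r = 0.1 to 0.3 the single-contrast gain is only 0.4 to 3.5 percentage points, and the 18% shift applies only at r = 0.5. This stands too, and is why a range is given.

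Three further inferences are tempting and not supported:
- That the QALY difference will be unadjusted. The article neither states nor excludes adjustment, and a condensed article may leave this to a fuller document.
- That every patient will have a baseline score on every scale. Questionnaires are scheduled, but the instruments sent at baseline are not itemised and missing data are foreseen.
- That the unadjusted model is the primary one. The sentence introducing the covariates can equally describe a single adjusted model.

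Finally, adjustment has conditions. Recruitment procedure has patients told their allocation before surgery, and the article does not say whether the baseline questionnaire comes before that. A score given after disclosure would be a questionable covariate.

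What survives is that the named covariate list omits the baseline value of the primary outcome, and that including it would improve the analysis at little cost.

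**Conclusion.** The point holds as an efficiency improvement. The primary model gives up whatever precision baseline EQ-5D-5L offers and leaves chance imbalance in the realised estimate. The stated sample size stands and the planned estimate is valid.

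On the plan's single contrast the gain runs from 0.4 points of power at r = 0.1 to 9.7 points at r = 0.5 (90.3% against 80.6%). The shift from a one-standard-error imbalance runs from about 0.003 to 0.014 against a target of 0.08. These sizes rest on assumed correlations, an assumed baseline SD of 0.15 and a two-sided test. The direction does not depend on the value of r: apart from the single degree of freedom, the gain is positive whenever r is not zero. For QALYs there is only something to confirm.

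**What to change.** In Primary study parameter, name one prespecified primary model that includes the baseline EQ-5D-5L index together with BMI, age and sex. Baseline can enter as a covariate, or through a constrained longitudinal model in which baseline is part of the outcome vector and the arms share one baseline mean. State that the baseline score is obtained before allocation is disclosed, and that missing baseline values are handled by the imputation already planned under Descriptive statistics. Do the same for each continuous patient-reported scale that is collected at baseline.

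In Economic evaluation, or in the document that governs it, confirm whether the QALY difference is adjusted for the baseline index.

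The cost is a short change of wording, one degree of freedom and the handling of a few missing baseline values. No new questionnaire is needed if the EQ-5D-5L is among the instruments sent at baseline. The change should be made before unblinded data are seen, so that the choice of model cannot appear to follow the result.
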